
## Methods

### Design

This is a three-arm single center pilot randomized trial with allocation ratio of 1:1:1. The arms are: (A) control, in which participants are provided with written materials about the benefits of physical activity; (B) text-messaging intervention, where participants receive multiple motivational messages from an automated, data-driven algorithmic text message program via mobile phone (*Coachtext*); and (C) voice-assist intervention, in which participants are provided with an in-home autonomous Intelligent Agent using data driven Interactive Digital Voice Assist on the Amazon Alexa/Echo (*MyCoach*).The trial duration is 5 weeks – a one-week run-in phase to establish baseline physical activity, followed by 4 weeks of intervention (Figure 1). Physical activity outcomes are captured via wearable sensors (Fitbit Charge 2 HR). Table 1 includes a schedule of enrollment, interventions, and assessments.

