### Study Outcomes

The aim of this study is to assess the effectiveness of different technological approaches in increasing physical activity among overweight and/or obese cancer survivors captured by wearable sensors (Fitbit Charge 2 HR). The primary outcome is the percent change in daily steps from the 1-week run-in to the end of the 4-week intervention period. The data for the primary aim is collected in real-time and transferred simultaneously to the computational server of the Johns Hopkins University via an application programming interface (API) that directly transmits the data from the user’s wearable device to the server. Participant wear-time is validated using the heart rate sensor readings on a minute-by-minute basis.

In addition to the primary outcome, the study will examine the following secondary outcomes: 1) total number and duration of activity bouts (defined as 3 minutes or more of uninterrupted activity); 2) fragmentation indices (counting transitions between active/inactive periods) and variability indices (counting the magnitude of transitions between different levels of physical activity); 3) daily diurnal patterns of activity that model patterns in minute-by-minute profiles; and 4) weekly and daily trends of total steps. Levels of physical activity intensity will be defined using each participant’s personalized heart rate reserve.

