### Statistical Analyses

As the primary outcome variable is the 4-week change from the baseline in the average number of steps per day, the primary analysis will use a two-sample t-test to compare each active intervention arm with the control arm based on intent-to-treat strategy. A Bonferroni correction will be used to adjust for multiple comparisons.

For the secondary outcomes (activities bouts, fragmentation, and patterns), a linear regression model will be fitted for the 4-week change from the baseline in the number of steps and duration of activity bouts each day. The independent variables include the baseline number of steps, study arm (modeled by two dummy variables for the two active treatment arms, and the control arm is treated as reference group), and any potential baseline confounding factors. Poisson regression will be used to analyze the total number of activity bouts, fragmentation indices, and variability indices. The independent variables include baseline number of steps, study arm, and any potential baseline confounding factors as the independent variables. In all analyses, data will be properly transformed to fit the model assumption before regression analysis. Although missing data is not anticipated to be a challenge, small amount of non-wear time for charging, bathing, etc. will have minimal effects on the primary study aim since it depends on the average steps across the intervention period. Since Stratified Permuted Block Randomization is being employed, we will consider minimization to balance interventions simultaneously over several prognostic factors to ensure equal distribution across arms. To date nearly 80% of the target population has been enrolled, and only one participant stopped wearing the tracker one day a week for religious reasons.

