## Discussion

### Study Rationale

This study designed, developed, and launched a clinical trial to investigate the effect of novel emerging technologies to assist cancer survivors to become more active in their daily lives. The study uses innovative technology and methods to apply autonomous artificial intelligent agents as an intervention. This is an affordable, scalable, and easily deployed personalized and tailored intervention that has the potential to transition from the research setting to general use. It is important to offer a scalable and affordable solution that can assist cancer survivors to become more active. Given the wide general utility of the technology and applicability of the outcome of interest, this approach may also be applicable to the general population with slight modification of the intervention and testing in a larger population study.

The trial operation is minimalist in design and effort. Recruitment activities and enrollment were designed and developed with a focus on low cost and efficiency. The study team developed innovative prescreening in the EMR environment, with remote intervention deployment and data collection processes. The entire trial is operated by the PI and the study coordinator. Data collection processing is autonomous and no interference from the study team or participants is needed. The data flow on a minute-by-minute basis to a structured database for real time analysis allows decision support for the artificial intelligent agent. The same data will be used subsequently to assess the effect of the intervention on the primary outcome. The trial’s recruitment is currently active and eligible consented patients have been enrolled.

Intelligent Agents (IA) are not new. Stuart Russell and Peter Norvig researched this topic extensively in their leading textbook in Artificial Intelligence—Artificial Intelligence: A Modern Approach [18]. Russell and Norvig state that the core behavior of an agent is goal-directed and therefore they refer to agents as “Rational Agents”. These agents can be classified into five classes: simple reflex agents, model-based reflex agents, goal-based agents, utility-based agents, and learning agents [18]. Amazon Alexa and our agent (*MyCoach*) use a combination of different agent classes. The study team chose to use different classes to adapt to the user’s intents.

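### The Poisson models for bout count, fragmentation and variability name baseline steps, not the outcome's own run-in value, as baseline covariate, which loses precision at 14 per arm

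*Protocol article*

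**What the plan says.** The Design section describes "a one-week run-in phase to establish baseline physical activity, followed by 4 weeks of intervention". Study Outcomes lists as secondary "total number and duration of activity bouts (defined as 3 minutes or more of uninterrupted activity") and "fragmentation indices (counting transitions between active/inactive periods) and variability indices (counting the magnitude of transitions between different levels of physical activity").

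Statistical Analyses then sets two kinds of model for these outcomes:

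- **Linear regression.** "a linear regression model will be fitted for the 4-week change from the baseline in the number of steps and duration of activity bouts each" (that is, per day). Its covariates: "The independent variables include the baseline number of steps, study arm (modeled by two dummy variables for the two active treatment arms", control being the reference), plus unspecified baseline confounders.
- **Poisson regression.** "Poisson regression will be used to analyze the total number of activity bouts, fragmentation indices, and variability indices". Its covariates: "The independent variables include baseline number of steps, study arm, and any potential baseline confounding factors as the independent variables". Nothing says that these outcomes are expressed as change from the run-in.

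On the data, Study Rationale states: "The data flow on a minute-by-minute basis to a structured database for real time analysis". All three arms wear the same tracker (Intervention section).

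**The concern.** In a small trial, the best single predictor of a participant's bout count or fragmentation index during the intervention is usually the same quantity in the run-in week. For the three Poisson outcomes the plan names it neither as a covariate nor, through a change score, as part of the outcome. It names baseline steps instead. Steps measure how much a person moves. The bout and transition measures describe how that movement is spread over the day, and the same daily total can come from a few long bouts or many short ones.

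The plan is also uneven. Bout number and bout duration are listed together as one secondary outcome, yet duration has its run-in value subtracted and number does not. No reason is given.

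At stake is the precision of the arm contrasts for these outcomes, and how far a chance difference in habitual pattern between arms shows up in the estimate. Randomization is stratified by sex, age group and BMI, not by activity, so the design does not balance these measures.

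**Working it through.** The article gives no precision figure for these outcomes, so there is none to reproduce. The one planned number used is 14 per arm (Sample Size). How that number was derived does not affect this point.

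**Assumed inputs (not in the article).** r is the correlation of the measure's run-in value with run-in steps, taken as 0.3 to 0.9. ρ is the correlation of the measure's run-in value with its follow-up value, taken as 0.8 or 0.5. Steps are assumed to add nothing once the own run-in value is known. Values are in between-person SD units.

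**1. Chance difference between two arms at baseline.** SD = √(2/14) = 0.378. Before any adjustment, a difference above 0.5 SD has probability P(|Z| > 0.5/0.378) = 18.6%.

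**2. What is left after adjusting for steps.** SD = √[(2/14)(1 − r²)]. The part that reaches the estimated arm effect for an outcome not expressed as change is ρ times this.

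**3. Variance of the arm effect, steps only against own run-in value added.** Ratio = (1 − ρ²r²)/(1 − ρ²). Example, ρ = 0.8 and r = 0.5: (1 − 0.16)/(1 − 0.64) = 0.84/0.36 = 2.33.

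| r | 0.3 | 0.5 | 0.7 | 0.9 |
|---|---|---|---|---|
| Leftover baseline difference, SD | 0.361 | 0.327 | 0.270 | 0.165 |
| Probability that it exceeds 0.5 SD | 16.6% | 12.7% | 6.4% | 0.2% |
| Part reaching the arm effect, ρ = 0.8 | 0.29 | 0.26 | 0.22 | 0.13 |
| Variance ratio, ρ = 0.8 | 2.62 | 2.33 | 1.91 | 1.34 |
| Variance ratio, ρ = 0.5 | 1.30 | 1.25 | 1.17 | 1.06 |

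**4. Check in Poisson models.** Step 3 is linear-model algebra, so it was checked by simulation: overdispersed counts, three arms of 14, ρ = 0.8, between-person SD of 0.5 on the log scale, 1,500 runs for each r. For r = 0.3, 0.5, 0.7 and 0.9:

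- The variance ratios were 2.29, 1.98, 1.69 and 1.21, somewhat below the formula but of the same order.
- The correlation of the estimated arm effect with the chance difference in the own run-in value fell from 0.70, 0.60, 0.45 and 0.18 (steps only) to 0.08, 0.04, 0.06 and 0.02 (own value added).
- The mean estimated arm effect was within 0.01 of zero under both models, so neither is biased on average.

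**5. Bout duration, a change score.** Variance given steps = (1 − ρ)²(1 − r²) + 1 − ρ²; with the own run-in value it is 1 − ρ². Take ρ = 0.7 and a correlation of 0.4 between baseline steps and follow-up duration, so r = 0.4/0.7 = 0.57. Then 0.09 × 0.673 + 0.51 = 0.571 against 0.51, and √(0.51/0.571) = 0.945: a standard error about 5% smaller. For 0.6 with 0.5 the result is √(0.64/0.689) = 0.964, and for 0.8 with 0.3 it is √(0.36/0.394) = 0.955, so about 4 to 5% in all three cases. Over r = 0.3 to 0.9 the variance ratio is 1.10 to 1.02 at ρ = 0.8. It rises to 1.30 to 1.06 at ρ = 0.5, where subtracting the baseline helps least.

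**The case against.** The strongest reply is that the covariate list is open. Both models admit unspecified baseline confounders, the own run-in value is an obvious candidate, and a journal article may leave the final list to a fuller plan. This stands to the extent that the article does not exclude the run-in value. It does not remove the point: the article chooses to name a baseline activity covariate and names steps, and the open phrase commits the analyst to nothing.

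A reader might infer three stronger things that the documents do not support:

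- **That the arm effects are biased.** Under randomization they are not, on average. Chance imbalance is part of the sampling error that a correct standard error covers. The loss is in precision and in the estimate from the one sample obtained.
- **That all the bout outcomes suffer alike.** Bout duration has its run-in value subtracted. Only regression to the mean remains.
- **That a half-SD imbalance passes through in about 19% of comparisons.** That figure is before adjustment. The planned steps covariate already removes part of the imbalance, and nearly all of the large ones if r is near 0.9.

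It is also fair to say that these are secondary outcomes of a pilot and that the primary t-test is untouched. Finally, Table 1 places the run-in after allocation, so adjusting for any run-in measure presumes that knowledge of the arm did not alter run-in behaviour. That applies equally to baseline steps and is no argument for steps over the own run-in value.

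**Conclusion.** The point holds for the total number of bouts, the fragmentation indices and the variability indices. As written, their models do not commit to the run-in value of the outcome, and the covariate named in its place is a partial proxy. The loss is moderate to large if these measures are stable within a person (variance about 1.3 to 2.6 times at ρ = 0.8; 1.2 to 2.3 in the simulation) and small to moderate if they are not (about 1.06 to 1.3 times at ρ = 0.5). It is smallest where the measure tracks steps closely. All of these sizes rest on assumed correlations; only the 14 per arm comes from the article. For bout duration the gain is about 4 to 5% of the standard error under the correlations in step 5, and larger only if ρ is low. This is an improvement in efficiency that needs no new data. It is not an error that invalidates the analysis, and it does not touch the primary outcome.

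**What to change.** In each model for bout number, bout duration, fragmentation and variability, prespecify the run-in value of that same outcome as the baseline covariate. Compute it by the same algorithm as the follow-up value and express it per day. In the count models enter it on the log scale, with a stated rule for a zero count. The step model already uses its own baseline and needs no change.

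Whether baseline steps stay in as a second covariate is open; nothing in the article requires dropping them. The choice should be written down before the blinded analyst starts.

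The cost is a change of wording. Replacing steps loses no degrees of freedom. Keeping both uses one more: with 42 participants, an intercept, two arm terms and one baseline covariate leave 42 − 4 = 38 residual degrees of freedom, and two baseline covariates leave 37, before any other confounders.

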## Discussion

### Study Rationale

This study designed, developed, and launched a clinical trial to investigate the effect of novel emerging technologies to assist cancer survivors to become more active in their daily lives. The study uses innovative technology and methods to apply autonomous artificial intelligent agents as an intervention. This is an affordable, scalable, and easily deployed personalized and tailored intervention that has the potential to transition from the research setting to general use. It is important to offer a scalable and affordable solution that can assist cancer survivors to become more active. Given the wide general utility of the technology and applicability of the outcome of interest, this approach may also be applicable to the general population with slight modification of the intervention and testing in a larger population study.

The trial operation is minimalist in design and effort. Recruitment activities and enrollment were designed and developed with a focus on low cost and efficiency. The study team developed innovative prescreening in the EMR environment, with remote intervention deployment and data collection processes. The entire trial is operated by the PI and the study coordinator. Data collection processing is autonomous and no interference from the study team or participants is needed. The data flow on a minute-by-minute basis to a structured database for real time analysis allows decision support for the artificial intelligent agent. The same data will be used subsequently to assess the effect of the intervention on the primary outcome. The trial’s recruitment is currently active and eligible consented patients have been enrolled.

Intelligent Agents (IA) are not new. Stuart Russell and Peter Norvig researched this topic extensively in their leading textbook in Artificial Intelligence—Artificial Intelligence: A Modern Approach [18]. Russell and Norvig state that the core behavior of an agent is goal-directed and therefore they refer to agents as “Rational Agents”. These agents can be classified into five classes: simple reflex agents, model-based reflex agents, goal-based agents, utility-based agents, and learning agents [18]. Amazon Alexa and our agent (*MyCoach*) use a combination of different agent classes. The study team chose to use different classes to adapt to the user’s intents.

Artificial intelligence (AI) has promising wide applications in translational research. Enablers to use such technologies, including tools and developer kits, are widely available for interested researchers, while codes libraries are shared among most researchers and powerful platforms are widely used in the form of mobile devices and home speakers. The current study provides insight beyond the target outcomes by its efficient operation. The entire study is operated by 1-2 persons. This is possible because most of the study components, including data collection, have been automated or enhanced by technology solutions. Even the start of the intervention is automated. The study team also automated the instructional communication via scheduled automated emails based on each participant enrollment date. The written consent process is still in paper format, a requirement of the University IRB.

In summary, the current trial demonstrates a very effective and efficient model for intervention that holds the potential to substantially change the way interventions are applied, monitored, and analyzed . The study has been design, developed and launched within the projected cost and timeline. However, challenges still exist. The main challenge for adopting such technologies include understanding the technology’s limitations; how behavioral theories can be adapted to human-machine interaction; limited funding sources for such research; privacy concerns; and the limited aggregable performance metrics for such technologies. Developing such interventions requires in-depth knowledge of AI and their operations, specifically programming. Most of the available behavioral change theories have been developed without consideration of human machine interaction and the potential limitations of such interactions. There are also still concerns about the stability and confidentiality surrounding AI in general, particularly in a health care setting; thus, there is no standardization for adopting AI technologies as there is for traditional interventions. As a result, the design concept for adapting the health coach functions to the AI machine was not straightforward. The user experience aspect was not traditional since no interface currently exists, and voice detection was the main interaction method. It was difficult to orchestrate different components, devices, and algorithms and to develop a secure environment/platform for transferring data within the requirements of the IRB. As a result, it was necessary to build our own server and connect all devices and databases via secure APIs. Further, the study team also overcome the security concerns by building creative solutions including transferring the decision of data transmission and devices communication into the hands of the participants in a form of electronic permissions and unique credentials. Lessons from this study are already helping to develop a more advanced Intelligent Agent to tackle common chronic conditions that rely on self-management and coaching and provide evidence that advancement in technology can be an agent of change to improve health outcomes.

### Trial Status

The study was approved as IRB #IRB00113882 on March 16, 2017. Recruitment activities were initiated in late April 2017. We started with targeted advertisements throughout Johns Hopkins oncology outpatient clinics. We also started active prescreening on Epic EMR to pre-identify participant prior to clinical encounter. The protocol went through a revision to refine the definition of physically active in the inclusion criteria using the American Heart Association definition of physically active. The recruitment activities are expected to last until March 2018. As of January 2018, we screened 75 patients and 39 are already enrolled in the study.

## Appendix

Multimedia Appendix 1 Dashboard for tracking user machine interaction.

Multimedia Appendix 2 Detailed peer review reports and responses by the scientific review committee at the SKCCC.

## Abbreviations

AI: artificial intelligence
API: application programming interface
CRC: Clinical Research Review Committee
CRMS: clinical research management system
EMR: electronic medical records
IA: intelligent agents
ICF: informed consent form
IRB: Institutional Review Board
IT: information technology
JHU: Johns Hopkins University
NCI: National Cancer Institute
NLP: natural language processing
PATH: Physical Activity by Technology Help
PI: principal investigator
SKCCC: Sidney Kimmel Comprehensive Cancer Center
